## Background

Hip fracture (HF) is highly prevalent in Spain, mainly affecting the elderly. It is estimated that 0.7% of women 65 years or older will suffer a hip fracture during their lifetime, and demographic trends predict that the demand for care will double in the next 40 years [1-3]. A total of 4-8% of these patients will die during hospitalization, and fewer than 25% will regain mobility and preserve autonomy at hospital discharge [4,5]. Socioeconomic burden associated to HF is enormous (40.000 euros (57.000 US dollars)) per patient [6].

Anemia is the one of the most frequent complications of HF; around one third to one half of patients will require red-cell pack(s) (RCP) transfusion [7]. RCP transfusion has been the classical choice in treating severe anemia of these patients [7]. Nevertheless, as already stated, the increasing incidence of HF in this population has also raised the need for this valuable and scarce resource. Additionally, RCP transfusions are not without complications [8-11]. In very old and often fragile patients, these effects may involve excess morbidity and mortality, making it necessary to develop blood-saving strategies (BSS) [9,12].

The most important factor in the development of anemia is blood loss, but some other mechanisms (renal failure, inflammation, iatrogenic hemodilution) are also implicated, prompting the choice of different therapeutic approaches [9,13,14]. These rely in three cornerstones: firstly minimizing blood loss in the operating room, secondly rationalizing RCP transfusion protocols, and thirdly enhancing bone-marrow red blood cell production [13-16]. Although evidence that this last measure saves RCP is weak, an increasing number of works have demonstrated notable reductions in RPC transfusion, nosocomial infections, hospital stay, and even survival [14-16]. Nevertheless, some biases in the nature of said studies could partly explain some of the obtained results.

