### Withdrawal from the study

Each participant will have the right to withdraw from the study at any time. In addition, the investigator may remove a participant from the study at any time if it is considered necessary for any reason including: significant protocol deviation, significant non-compliance with treatment regimen or study requirements, an adverse event which requires discontinuation of the study medication or results, inability to continue to comply with study procedures, consent withdrawn, and loss of follow up.

All the patients leaving the study will fulfill the described procedures of premature finalization as described in the protocol. The analysis will be carried out for all the patients who have received a dose of experimental medicine or control.

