### Outcome measures

The primary outcome measure will be the percentage of patients who receive red-cell transfusion during hospitalization, and after 60 days of hospital discharge.

Secondary outcome measures will be the following related with efficacy, safety, HRQoL, and cost-effectiveness

Efficacy end-points: the average number of red-cell packs needed per patient at the end of the study, the average number of red-cell packs needed per patient (only transfused patients), the average hemoglobin level at 24 and 72 hours postoperative period and at hospital discharge, and the total number of hospitalization days.

Safety endpoints: the death rate from all causes at the end of the study; and adverse events including the following clinical complications: vascular events, all kinds of cerebrovascular accidents, acute coronary syndrome, thrombosis, arterial embolism, heart failure, acute/chronic exacerbation of respiratory failure, delirium, thromboembolic disease, catheter-related phlebitis; renal failure; infectious complications: pneumonia, urinary tract infection, surgical-site infection; and all side effects detailed on the EPO and FC data sheet.

HRQoL end-point: Quality of life will be assessed by the Short form 36 version 2 (SF-36) for acute patients [20]. This questionnaire will be administered at inclusion and 60 days after hospital discharge.

Cost-effectiveness end-point: An analysis of incremental cost-effectiveness (using as a primary endpoint each patient not requiring a transfusion, and as a secondary endpoint every patient who survived the index admission) will be performed.

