### Statistical analysis

Both intention to treat (ITT) and per protocol analysis will be performed. The ITT analysis will include all patients who agreed to participate in the study, signed the informed consent, and had been randomized. Per protocol analysis will include the patients who were randomized, received the dose of erythropoietin and ferric carboxymaltose (EPOFE arm), ferric carboxymaltose (FE arm), or placebo (PLACEBO arm), and were operated on; excluding those who discontinued the trial, or received a red-cell pack in a different format than specified in the protocol. Violation of the blinded assignment will be also excluded in the per protocol analysis.

A chi-square test will be performed in order to establish the comparative analysis of the primary efficacy outcome, secondary efficacy, safety and cost endpoints between different arms of the study (Yates correction and, where necessary, Fisher exact test) for qualitative endpoints. Analysis of variance (with post-hoc test of Tukey and T3-Dunette)/Kruskal-Wallis test will be performed for quantitative variables. Differences between groups will be quantified using 95% confidence intervals.

The cost-effectiveness analysis will be performed by incremental cost-effectiveness method, using each patient who did not require RCP transfusion as the primary efficacy unit; each patient surviving at discharge and 60 days after discharge as the high efficiency unit; and the sum of all previously recorded costs of hospitalization as the cost unit. The calculations will be performed as follows: incremental cost-effectiveness (Euros per unit of efficiency gains) = NNT × (cost per a) option patient - cost per b) option patient).

All calculations will be performed using SPSS 18.0. The threshold of statistical significance is set at *p *< 0.05.

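### The SF-36 is measured at inclusion and at 60 days, but the only stated test for a numeric score does not adjust for the inclusion value, so precision already paid for is given up

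*Protocol article*

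**What the plan says.** Under Outcome measures, the protocol article lists health-related quality of life as one of four classes of secondary outcome. The instrument is fixed: "Quality of life will be assessed by the Short form 36 version 2 (SF-36) for acute patients". So is the timing: "This questionnaire will be administered at inclusion and 60 days after hospital discharge". The article does not say which SF-36 scale is analysed, or whether the compared quantity is the 60-day score or the change from inclusion.

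Under Statistical analysis, quality of life is not mentioned by name. Efficacy, safety and cost end-points are named in the sentence on chi-square tests for qualitative end-points. Numeric outcomes come under one general rule: "Analysis of variance (with post-hoc test of Tukey and T3-Dunette)/Kruskal-Wallis test will be performed for quantitative variables". The article adds that "Differences between groups will be quantified using 95% confidence intervals". No covariate is mentioned for any analysis.

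Under Methods, the randomisation list is stratified by centre.

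**The concern.** When the same questionnaire is given before treatment and at the end, the early score usually explains part of the spread in the late score. A one-way comparison of late scores leaves that spread in the error term. A one-way comparison of changes removes some of it, but adds the noise of the inclusion score when the two scores are only weakly related. ANCOVA estimates the right weight from the data and avoids both losses.

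What is at stake is the width of the intervals on a secondary end-point. The sample size was set for transfusion, with no provision for the SF-36, so precision available at no recruitment cost is worth having. The unadjusted comparison is not invalid: under randomisation it estimates the same difference, only less sharply.

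**Working it through.** **The plan's own figure.** The article gives no SF-36 standard deviation, effect size or power, so there is no SF-36 figure to reproduce. Its only sample-size figure is 87 evaluable patients per arm for transfusion (60% against 40%, one-sided 5%, 80% power). Without continuity correction:

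(1.645·√(2·0.5·0.5) + 0.842·√(0.24 + 0.24))² / 0.20² ≈ 76.2, rounded up to 77.

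With the correction: 76.2/4 · (1 + √(1 + 4/(76.2·0.20)))² ≈ 86. This agrees with 87 to within one patient, and 87/0.85 = 102.35, which the article states as 102. The 87 is used below only as a plausible number of scores per arm. The variance ratios do not depend on it.

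**Inputs.**
- Two SF-36 measurements: Outcome measures.
- Unadjusted one-way test: Statistical analysis.
- 87 per arm: Sample size calculation.
- Correlation r between inclusion and 60-day score: not in the documents; assumed 0.3, 0.5 and 0.7.
- Unit: the standard deviation of the 60-day score, taken as equal at both times and in all arms.

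**Relative variance of a difference between two arms.**
- 60-day score, unadjusted: 1
- Change from inclusion: 2(1 − r)
- ANCOVA on the inclusion score: 1 − r²

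**Half-width of the 95% interval for one pair of arms:** 1.96·√(2·v/87), where v is the relative variance. For v = 1 this is 1.96·0.1516 = 0.297 SD.

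| r | v, 60-day | v, change | v, ANCOVA | half-width, 60-day | half-width, change | half-width, ANCOVA | patients per arm for an unadjusted 60-day comparison to match, 87/(1 − r²) |
|---|---|---|---|---|---|---|---|
| 0.3 | 1 | 1.4 | 0.91 | 0.297 | 0.352 | 0.283 | 95.6 |
| 0.5 | 1 | 1.0 | 0.75 | 0.297 | 0.297 | 0.257 | 116.0 |
| 0.7 | 1 | 0.6 | 0.51 | 0.297 | 0.230 | 0.212 | 170.6 |

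**Does the ordering depend on the assumed r?** No. Against the 60-day score, ANCOVA saves 1 − (1 − r²) = r², which is never negative. Against the change score it saves 2(1 − r) − (1 − r²) = (1 − r)², which is never negative either. If the inclusion SD is k times the 60-day SD, the change variance becomes 1 + k² − 2rk and the saving (k − r)², so the ordering survives unequal spreads. Only the size of the gain depends on r.

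**Limits.** The formulas describe the analysis-of-variance route; the Kruskal-Wallis test has no equally simple expression, but it too uses no covariate. The half-widths are for a single pair. A multiplicity adjustment such as Tukey's widens all three in the same proportion. The one degree of freedom spent on the covariate is negligible at this size.

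**The case against.** **A journal article condenses.** Covariates and choice of scale for a secondary questionnaire are commonly left to the full protocol or analysis plan, neither of which is shown. That has force: not naming the scale is no finding by itself. But the article is not merely silent on method. It states a test for quantitative variables, and that test has no adjustment. If the full plan already specifies ANCOVA, the article's wording needs only to be brought into line.

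**A change score is not excluded.** True, so one cannot say that the inclusion score is ignored. The point survives because ANCOVA is at least as precise as either reading, and at r = 0.3 the change score is worse than leaving the inclusion score out.

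**It is an efficiency preference, and the gain may be small.** Also fair. The inclusion questionnaire is completed after admission with a fracture, so r could be low. At r = 0.3 the half-width falls only from 0.297 to 0.283 SD.

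**A stronger reading is tempting.** A reader might infer that patients who die are dropped, so that the result leans toward the arm with more deaths. The background gives a reason to ask: "A total of 4-8% of these patients will die during hospitalization". But the article does not say that deaths are dropped or that only available scores are compared. It defines its intention-to-treat set as all randomised patients, gives no mortality by arm, and analyses death separately as a safety end-point. A lean needs three things together: a survivors-only comparison, unequal deaths, and deaths among patients who would have scored low. In a normal model with death proportion d, frailty-score correlation c, and z_d the normal quantile of d, the survivor mean shifts by c·φ(z_d)/(1 − d).
- Deaths of 4% against 8%, with c = 0.3 or 0.5: (0.162 − 0.090)·c = 0.02 or 0.04 SD.
- An assumed 10% against 20%, with c = 0.7: (0.350 − 0.195)·0.7 = 0.11 SD.
- Equal deaths or c = 0: no lean.

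The standard error of a two-arm difference is √(2/87) = 0.15 SD, so each of these is below one standard error. The direction is not fixed in favour of treatment either. Lower mortality is among the aims in the abstract; if it were achieved, survivor selection would count against the active arms.

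**Conclusion.** The point holds as one of precision. The stated one-way comparison does not adjust for an inclusion score that the trial collects. Under either reading of the analysed quantity it is less precise than ANCOVA, except in the limiting cases: r = 0 for the 60-day score, or r equal to the SD ratio k (r = 1 when the spreads are equal) for the change score. For assumed r from 0.3 to 0.7, the unadjusted 60-day comparison has 9% to 49% more variance to remove, measured against its own variance. The ordering does not rest on r, but the size does, and the documents give no value.

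The point does not extend to a claim that the quality-of-life result is biased. The documents do not fix the handling of deaths, and under the assumptions tried any lean is small. This is a modest improvement to a secondary end-point and does not touch the transfusion analysis.

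**What to change.** In Statistical analysis, add a sentence to this effect:

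> The 60-day SF-36 score [scale to be named by the sponsor] will be compared between arms by analysis of covariance with the inclusion score and centre as covariates, giving multiplicity-adjusted pairwise differences with 95% confidence intervals. The numbers of patients dead and unassessed at 60 days will be reported by arm beside this result.

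Centre is included because randomisation is stratified by it. The sponsor should choose the scale; nothing in the article points to one.

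A Kruskal-Wallis test that ranks deaths below every observed score is at most an optional sensitivity analysis. It mixes death with quality of life, so it would stand beside the adjusted estimate and not replace it.

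The cost is wording only, with no new data and no extra patients. One practical consequence is that a patient without an inclusion score cannot enter the adjusted model unless a rule for that is stated; a change-score analysis would have the same need. The change should be made before arm-level data are seen.

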### Sample size calculation

Sample size was calculated as follows:

-To obtain statistical significance in the comparison between the i.v. iron + EPO arm compared to placebo. The treatment arm exclusively with iron is only used in the evaluation of results, but not in the sample size calculation.

-To obtain a confidence level of 95% and 80% power.

-To be single sided.

-To obtain a reduction in the primary endpoint of 20% (percentage of patients who need transfusions), which is considered as clinically significant in the literature. According to this, we would expect the percentage of patients who need to be transfused in the placebo group to be 60% and in the treatment group 40%.

-Sample size was calculated online using SISA http://www.quantitativeskills.com/sisa/calculations/samsize.htm. A total of 87 patients per arm are needed with the foregoing conditions.

-Taking into account a percentage of drop-outs of 15% per arm, the total number of patients per arm is set at 87 × (1/1-0.15) = 102, a total of 306 patients.

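### The sample size is one-sided at 5%, but the planned primary analysis reads as two-sided at 5%, so power at the planned 87 evaluable per arm is about 73–78%, not 80%

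*Protocol article*

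**What the plan says.** In the protocol article, Sample size calculation sizes one contrast only, the "comparison between the i.v. iron + EPO arm compared to placebo". Its conditions are "To obtain a confidence level of 95% and 80% power", then "To be single sided", with the proportion "transfused in the placebo group to be 60% and in the treatment group 40"%. The result is "A total of 87 patients per arm are needed with the foregoing conditions". The next line, "Taking into account a percentage of drop-outs of 15% per arm", raises this to 102 per arm and 306 in total.

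Statistical analysis tests the primary outcome with a chi-square test, adding "Yates correction and, where necessary, Fisher exact test) for qualitative endpoints". It continues: "Differences between groups will be quantified using 95% confidence intervals". The significance threshold is p < 0.05. The section does not use the terms one-sided or two-sided, and gives no one-sided bound, halved p-value or 90% interval.

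**The concern.** A chi-square statistic squares the difference between arms, so it rejects for a difference in either direction. Taken at p < 0.05 and paired with an ordinary 95% interval, it is a two-sided 5% procedure. The sample size rests on a one-sided 5% test, which has a lower critical value. If the analysis is run as written, the number of patients was computed for an easier test than the one that decides the trial.

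Two things are at stake. The stated 80% power may not belong to the planned analysis. The article also supports two decision rules for the primary endpoint: a favourable result with a chi-square p-value between 0.05 and 0.10 succeeds under the sizing rule and fails under the analysis rule. If this is left open, the choice could be made with the result in view. The interim analysis, which also assesses the primary efficacy endpoint, inherits the same ambiguity.

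**Working it through.** **Inputs.** From Sample size calculation: p1 = 0.60, p2 = 0.40, difference d = 0.20, alpha = 0.05, power 0.80, 87 evaluable per arm, 15% drop-out, 102 randomised per arm. From Statistical analysis: chi-square test, p < 0.05, 95% intervals.

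**1. Reproduce the 87.** The pooled-variance formula per arm is

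n = [z_α √(2 p̄ q̄) + z_β √(p1q1 + p2q2)]² / d²

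with p̄ = q̄ = 0.50, so √(2 p̄ q̄) = √0.50 = 0.7071; √(p1q1 + p2q2) = √0.48 = 0.6928; z_β = 0.8416. The continuity-corrected size is n_c = (n/4)[1 + √(1 + 4/(n d))]².

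- One-sided 5% (z_α = 1.645): n = (1.163 + 0.583)² / 0.04 = 76.2. Corrected: n_c = 85.9, i.e. 86.
- Two-sided 5% (z_α = 1.960): n = (1.386 + 0.583)² / 0.04 = 96.9, i.e. 97. Corrected: n_c = 106.7, i.e. 107.

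Unpooled and arcsine versions without correction give 75 and 77 one-sided, and 95 and 97 two-sided. Of the variants tried, only the one-sided, continuity-corrected one comes within two patients of 87. The drop-out step also checks: 87 / (1 − 0.15) = 102.4, stated as 102. The arithmetic of the section is therefore sound on its own one-sided terms.

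**2. Power of the analysis as ordinarily read.** By normal approximation, without correction, at 87 per arm:

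(d√n − z_α × 0.7071) / 0.6928 = (1.8655 − 1.3859) / 0.6928 = 0.692, so power = 75.6%.

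The approximation is slightly low here. Summing the binomial probabilities of every 2×2 table that the test rejects gives exact power:

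| Evaluable per arm | Two-sided 5%, Pearson | Two-sided 5%, Yates | One-sided 5%, Pearson | One-sided 5%, Yates |
|---|---|---|---|---|
| 87 | 77.6% | 72.8% | 85.7% | 82.0% |
| 97 | 80.7% | 76.4% | 87.6% | 84.4% |
| 102 | 83.8% | 80.1% | 89.8% | 87.0% |

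At 87 per arm the two-sided type II error is 100 − 77.6 = 22.4% (Pearson) or 100 − 72.8 = 27.2% (Yates).

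**3. Where 80% is regained.** Two-sided Pearson power is just under 80% at 96 per arm (79.98%) and above it at 97, a loss of (102 − 97)/102 = 4.9%. With Yates, 101 per arm gives 79.4% and 102 gives 80.1%, so in effect every randomised patient must have an outcome.

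**4. How often the two rules disagree.** Under 60% vs 40% at 87 per arm, one-sided minus two-sided power is 82.0 − 72.8 = 9.2 points with Yates and 85.7 − 77.6 = 8.1 points with Pearson. In roughly one trial in eleven or twelve, the verdict would depend on which section is followed.

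**The case against.** The strongest reply is that the analysis section never says two-sided. The only statement on sidedness in the article is the one-sided condition, and it stands beside the comparison being powered. A 2×2 comparison can be tested directionally, by the signed root of chi-square or a one-sided Fisher test, and power at 87 is then 86% (Pearson) or 82% (Yates). An article may also leave the sidedness of a test to the full protocol or the analysis plan. This stands in part: two-sided is an inference from the test and intervals named, not a statement of the plan. It does not remove the point, because the directional reading appears nowhere in the analysis section and does not fit its ordinary 95% intervals. If a one-sided test was meant, that section still needs correcting.

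A second reply is that the intention-to-treat population is everyone randomised, 102 per arm, where two-sided power is 84% or 80%. This stands if outcomes are nearly complete. The plan itself allows for 15% loss, however, and the 80% claim is attached to the 87 who remain.

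A reader might also infer that the Yates correction is a further, unplanned loss of power. The documents do not support that: the 87 is matched only with a continuity correction, so sizing and analysis agree on it. Nor does the article say that the correction is routine for the primary test.

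**Conclusion.** The inconsistency is real and moderate. The sizing is one-sided at 5%; the analysis as ordinarily read is two-sided at 5%. At the planned 87 evaluable per arm, exact power is about 78% (Pearson) or 73% (Yates), which is 2 to 7 points below the stated 80%. The cause is the difference in sidedness.

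The conclusion rests on three conditions: the two-sided reading of the chi-square test and 95% intervals; loss of most of the allowed 15% (with Yates, even small losses suffice); and the plan's own 60% and 40%. A reader might go further and call the trial underpowered outright, or put the type II error as high as 30%. Neither is supported. With outcomes on all 102 per arm the two-sided test reaches 80–84%. The 30% comes from a cruder normal approximation for the corrected test (about 70% power), where exact enumeration gives 27%.

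**What to change.** Before unblinding, use one sidedness in both Sample size calculation and Statistical analysis.

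- **Preferred:** state that the primary comparison of iron plus erythropoietin with placebo is tested two-sided at 5%. Restate the power as about 73–78% at 87 evaluable per arm, depending on whether the continuity correction is applied, and about 80–84% if all 102 per arm have outcomes.
- **Alternative:** state in Statistical analysis that this primary test is one-sided at 5%, with a matching one-sided confidence bound. The 87 and the stated 80% then stand (82% exact with Yates).

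Either route changes wording only and adds no patients. The first costs a less favourable power statement. The second requires the one-sided error rate to be declared openly and the interval for the primary outcome to be changed. Holding a full 80% two-sided at 15% loss would instead need, by formula, 97 evaluable (115 randomised) per arm without correction or 107 (126 randomised) with it, i.e. 345 or 378 patients over three arms. Reconciling the two sections does not require that.

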### Statistical analysis

Both intention to treat (ITT) and per protocol analysis will be performed. The ITT analysis will include all patients who agreed to participate in the study, signed the informed consent, and had been randomized. Per protocol analysis will include the patients who were randomized, received the dose of erythropoietin and ferric carboxymaltose (EPOFE arm), ferric carboxymaltose (FE arm), or placebo (PLACEBO arm), and were operated on; excluding those who discontinued the trial, or received a red-cell pack in a different format than specified in the protocol. Violation of the blinded assignment will be also excluded in the per protocol analysis.

A chi-square test will be performed in order to establish the comparative analysis of the primary efficacy outcome, secondary efficacy, safety and cost endpoints between different arms of the study (Yates correction and, where necessary, Fisher exact test) for qualitative endpoints. Analysis of variance (with post-hoc test of Tukey and T3-Dunette)/Kruskal-Wallis test will be performed for quantitative variables. Differences between groups will be quantified using 95% confidence intervals.

The cost-effectiveness analysis will be performed by incremental cost-effectiveness method, using each patient who did not require RCP transfusion as the primary efficacy unit; each patient surviving at discharge and 60 days after discharge as the high efficiency unit; and the sum of all previously recorded costs of hospitalization as the cost unit. The calculations will be performed as follows: incremental cost-effectiveness (Euros per unit of efficiency gains) = NNT × (cost per a) option patient - cost per b) option patient).

All calculations will be performed using SPSS 18.0. The threshold of statistical significance is set at *p *< 0.05.

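### The per-protocol set excludes patients for the way they were transfused, which only patients with the primary event can meet, and the dosed-only sentence conflicts with the ITT definition

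*Protocol article*

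**What the plan says.** All references are to the protocol article.

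- **Outcome measures.** The primary outcome is the "percentage of patients who receive red-cell transfusion during hospitalization, and after 60 days of hospital discharge".
- **Statistical analysis, planned sets.** "Both intention to treat (ITT) and per protocol analysis will be performed". The first of these two sets is defined as follows: "The ITT analysis will include all patients who agreed to participate in the study, signed the informed consent, and had been randomized". Dosing is not a condition.
- **Statistical analysis, per-protocol set.** It requires randomisation, receipt of the allocated treatment and surgery. It leaves out patients who stopped the trial early and any who "received a red-cell pack in a different format than specified in the protocol". Patients whose blinded assignment was violated are also excluded.
- **Withdrawal from the study.** "The analysis will be carried out for all the patients who have received a dose of experimental medicine or control". The sentence names no analysis set and is not limited to safety.
- **Outcome measures, secondary efficacy.** Mean red-cell packs is listed twice: per patient at the end of the study, and per patient among transfused patients only.

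**The concern.** A per-protocol set may exclude patients for departures from the assigned treatment or procedures. Here one exclusion depends on a post-randomisation event that is itself the primary outcome. A patient who never receives a red-cell pack cannot receive one in the wrong format, so the clause takes patients out of the numerator and the denominator together and leaves every non-event in place. This is so however the full protocol defines the format. At stake is whether the per-protocol result can support the intention-to-treat result: it understates transfusion rates to the extent that the clause is applied, and its treatment contrast shifts if off-format transfusion is more common in one arm.

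The second issue is a conflict between two sections. Patients are randomised first and treated as soon as possible afterwards, before surgery (Methods). A patient can therefore be randomised and not dosed. That patient belongs to the intention-to-treat set but falls outside the dosed-only sentence.

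**Working it through.** **Inputs.** From Sample size calculation: 60% transfused on placebo, 40% in the combined-treatment (EPOFE) arm, one-sided 95% confidence, 80% power, 87 per arm, 15% drop-out, 102 per arm. The share f of transfused patients whose transfusion is off-format is not in the document. Values of 10% to 30% are assumptions.

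**The plan's own figure.** The one-sided two-proportion formula with continuity correction gives 86 per arm, against the stated 87. Drop-out: 87/(1 − 0.15) = 102.35, stated as 102. Neither is disputed.

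**Effect of the clause alone.** With true rate p, the clause removes a fraction pf of the arm, all of them events:

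per-protocol rate = p(1 − f)/(1 − pf)

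- p = 0.60, f = 0.20: 0.48/0.88 = 54.5%
- p = 0.40, f = 0.20: 0.32/0.92 = 34.8%

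The odds of transfusion are multiplied by (1 − f), so the odds ratio (placebo against EPOFE) becomes 2.25 × (1 − f placebo)/(1 − f EPOFE).

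| f placebo | f EPOFE | Placebo | EPOFE | Difference (points) | Odds ratio |
|---|---|---|---|---|---|
| 0 | 0 | 60.0% | 40.0% | 20.0 | 2.25 |
| 10% | 10% | 57.4% | 37.5% | 19.9 | 2.25 |
| 20% | 20% | 54.5% | 34.8% | 19.8 | 2.25 |
| 30% | 30% | 51.2% | 31.8% | 19.4 | 2.25 |
| 20% | 0 | 54.5% | 40.0% | 14.5 | 1.80 |
| 0 | 20% | 60.0% | 34.8% | 25.2 | 2.81 |

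**No true effect.** With 60% in both arms and f = 20% in one arm only, the rates are 54.5% and 60.0%, a spurious 5.5 points. Starting from 102 per arm, the affected arm keeps 102 × (1 − 0.12) = 89.8 patients. A two-sided 5% test (normal approximation, no continuity correction) then rejects in about 12% of trials instead of 5%.

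**The analysis populations, side by side.**

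| Patient | ITT (Statistical analysis) | Dosed-only sentence (Withdrawal) | Per protocol (Statistical analysis) |
|---|---|---|---|
| Randomised, not dosed | in | out | out |
| Dosed, not operated on | in | in | out |
| Dosed, operated on, off-format transfusion | in | in | out |

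The dosed-only population matches neither of the two named sets. Each undosed patient changes an arm's denominator by 1 in 102. The document gives no basis for their number.

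**Transfused-only mean.** At the planned rates this compares about 102 × 0.60 = 61 placebo patients with 102 × 0.40 = 41 EPOFE patients. Both groups are selected by the primary outcome, so the comparison is not a randomised one.

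**The case against.** The strongest reply is that the trial's main protection is intact. An all-randomised intention-to-treat analysis is planned and listed first, and it has no format exclusion. The trial is double-blind, with masked syringes and opaque infusion sets, so a large difference between arms in off-format transfusion is less likely. With equal shares the difference and the odds ratio hardly change. All of this stands, and it limits the weight of the point. Blinding does not guarantee equal shares, however: the treatments are meant to raise haemoglobin, so the circumstances of transfusion may differ by arm.

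A reader might infer that per-protocol rates must be too low overall. The document does not support that. The same set also drops patients who were not dosed, were not operated on or discontinued, and those exclusions can remove non-events. The downward direction belongs to this clause alone.

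A reader might also see two rival main analysis sets. The dosed-only sentence does not call its set main, and in its place it may only mean that dosed patients who leave are still analysed. Its wording is unrestricted, though, so the two sections need reconciling. That the article does not name a primary set is not held against it, because an analysis plan may do so.

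Finally, the statement that "the investigator may remove a participant from the study at any time if it is considered necessary" might suggest that outcomes are lost after a single-dose treatment. The article refers to premature-finalisation procedures in the full protocol and requires an end-of-study assessment after withdrawal for an adverse event. Nothing says that transfusion data stop being collected, and the 15% drop-out is not broken down by cause.

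**Conclusion.** The point holds for two stated rules. First, the format clause conditions the per-protocol set on the primary outcome and can delete only events. Its effect on the arm difference is negligible if off-format shares are equal (19.4 to 19.9 points for shares of 30% down to 10%) and material if they are not (14.5 or 25.2 points for 20% in one arm only). These sizes rest on assumed shares and isolate the clause from the other per-protocol exclusions. They show what the clause can do and do not predict what will happen. Only the per-protocol analysis is exposed. Second, the dosed-only sentence and the intention-to-treat definition give different populations for any randomised but undosed patient. That group is likely to be small, but it is not quantified.

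This should be corrected, but it does not undermine the trial. The transfused-only mean is a minor matter, since packs per patient is already a listed endpoint.

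**What to change.** 1. In Statistical analysis, delete the exclusion for red-cell packs given in a different format. Count any red-cell pack as a primary event in every analysis set, and report off-format transfusions in a table by arm.
2. In Withdrawal from the study, limit the dosed-only population to safety, and state that the primary efficacy comparison uses the all-randomised intention-to-treat set.
3. Minor: label the transfused-only mean number of packs as descriptive, and use packs per patient, zeros included, for the between-arm test.

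The cost is wording only. Sample size, visits and treatment are unchanged, and no transfusion rule is proposed or altered.
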